### Outcomes

The primary outcome will be the change in physical performance at the end of the follow-up, as assessed by the SPPB score, with a comparison between the control and intervention groups. Secondary outcomes will include changes in the performance of individual SPPB items (balance, gait speed, chair-stand test), changes in cognitive function as measured by MoCA scores, and the incidence or progression of ADL disability. Additionally, we will evaluate the incidence of sarcopenia, falls, and institutionalization. Lastly, other secondary outcomes will include hospitalization rates for all-cause and diabetes-related complications, changes in HbA1c levels, the number of days spent at home post-randomization (DAH), accounting for death, hospitalization, and new care home placement, and all-cause mortality rate.

### Sample size and statistical analysis

Using data from a previous observational study in older Italian patients with diabetes [29], we hypothesized a baseline mean SPPB score of 6.9 with a 1.8 standard deviation. Assuming that a difference of 1 SPPB score point is clinically meaningful [30], we estimated that 72 patients in each group would provide a 90% power at a 5% significance level to detect this difference between the intervention and the control group after 12 months from enrolment. To account for a 20% loss to follow-up, including patients who will die during the study follow-up, we planned to enroll 90 patients for each study group, for a total of 180 participants.

Data will be described as mean and standard deviation or median and interquartile range for continuous variables and frequency and percentage for categorical variables. Baseline characteristics will be compared between intervention and control groups using ANOVA for normally distributed continuous variables, nonparametric tests for non-normally distributed continuous variables, and chi-square or Fisher’s exact test for categorical variables.

Changes in SPPB scores (primary outcome) between study groups over follow-up will be assessed using longitudinal data analysis for repeated measures. Differences in secondary binary outcomes between groups will be analyzed using multivariable logistic regression models or Cox proportional hazard models, as appropriate. Changes in secondary continuous outcomes between groups will also be evaluated using longitudinal data analysis for repeated measures. All statistical models will be adjusted for relevant potential confounders, including socio-demographic factors, comorbidities, medications and study center. Confounders will be selected based on their association with the specific outcome being analyzed and consideration of collinearity. Comorbidities and medications will be incorporated into the models either as individual variables - when specific conditions or treatments are expected to influence the outcome - or as aggregated measures (e.g., total number of comorbidities or medications) to reflect overall disease or treatment burden, depending on their distribution and relevance. A two-tailed p-value < 0.05 will be considered statistically significant.

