### Recruitment and randomization

Trained researchers embedded in each diabetology outpatient unit will assess patients for inclusion and exclusion criteria. Those meeting the criteria will be invited to participate and asked to provide written informed consent. After the baseline assessment, participants will be randomly assigned to either the intervention or control group. A secure internet-based system will be used for randomization, assigning participants to the groups in a 1:1 allocation ratio, stratified by center. A total of 60 patients per center will be recruited, for a combined total of 180 participants.

Given the low-risk nature of the intervention, no data monitoring committee has been established for this trial. This approach has been approved by the Ethics Committees at all participating centers.

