### Interventions

Every recruited patient will receive standard care in accordance with current diabetes guidelines from a diabetologist. Additionally, a trained geriatric researcher will administer the CGA to patients in both the control and the intervention groups. For the intervention group, the CGA will be used to identify and optimize medical treatment concerning functional outcomes and PROMs. Specifically, the CGA will guide medication review and deprescribing, functional training, nutritional advice, and environmental adaptation. Specialist consultation will be recommended for hearing or visual impairments, and cognitive dysfunction (MoCA ES < 4), or in presence of anxiety or depressive symptoms. Patients in the control group will continue to receive standard care as per current guidelines for patients with T2DM, without additional interventions.

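### Covariates for the primary SPPB model are to be selected by association with the outcome, with coding left open and no restriction to baseline values, so the confirmatory model is not fixed

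*Protocol article*

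**What the plan says.** The Protocol article, under Sample size and statistical analysis, assigns the primary outcome to a longitudinal repeated-measures analysis and then sets one adjustment policy for everything: "All statistical models will be adjusted for relevant potential confounders, including socio-demographic factors, comorbidities, medications and study center". The primary SPPB model falls within it. The next sentence gives the selection rule: "Confounders will be selected based on their association with the specific outcome being analyzed and consideration of collinearity". A third sentence lets comorbidities and medications enter either one by one or as totals, according to how they are distributed and how relevant they are. No measurement time is given for any covariate. Significance is then declared by one criterion: "A two-tailed p-value < 0.05 will be considered statistically significant".

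Three other sections bear on this:
- **Recruitment and randomization:** the system works by "assigning participants to the groups in a 1:1 allocation ratio, stratified by center".
- **Interventions:** in the intervention group only, "the CGA will guide medication review and deprescribing, functional training, nutritional advice, and environmental adaptation".
- **Baseline assessment and Follow-up:** medication use is recorded at baseline, and the comorbidity index and pharmacotherapy are recorded again at 6 and 12 months.

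The Discussion calls the secondary outcomes exploratory, so the SPPB comparison is the trial's one confirmatory test.

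**The concern.** Searching for confounders by their association with the outcome belongs to observational research. Here randomization deals with confounding by design, and adjustment is there to gain precision and to reflect the stratification. Neither purpose needs a data-dependent search; both are met by naming a few baseline covariates beforehand.

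Two things are at stake.

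1. **A primary result that is not unique.** With the selection criterion and the coding both open, different analysts could follow the text faithfully and reach different primary models, each with its own p-value judged against 0.05.
2. **Conditioning on a consequence of treatment.** Medications are candidates, and the intervention sets out to change them. In a repeated-measures model with pharmacotherapy available at each visit, entering time-updated values would be easy and is not excluded. That would remove whatever part of the effect acts through deprescribing.

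**Working it through.** **Inputs from the Protocol article, Sample size and statistical analysis**
- Difference of 1 point: "Assuming that a difference of 1 SPPB score point is clinically meaningful".
- SD 1.8: "we hypothesized a baseline mean SPPB score of 6.9 with a 1.8 standard deviation".
- Size and power: "we estimated that 72 patients in each group would provide a 90% power at a 5% significance level".
- Two-sided 5% level; 20% loss to follow-up; 90 enrolled per group.

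**Step 1: reproduce the plan's figure.**
n = 2 × (1.960 + 1.282)² × 1.8² / 1² = 2 × 10.51 × 3.24 = 68.1, so 69 per group. The t-test gives 69.06, so 70. The plan's 72 is close to both. At 72 per group, SE = 1.8 × √(2/72) = 0.30, and power = Φ(1/0.30 − 1.96) = Φ(1.373) = 91.5% (t-test 91.2%). Allowing for loss, 72/0.8 = 90 per group and 180 in total. The sample size holds and this point does not change it.

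**Step 2: type I error under different uses of the selection rule.**
Null trials were simulated with 72 per arm and an ordinary linear model. The number and strength of covariates are assumptions, since the article gives neither.

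| Use of the rule | Assumed candidates | Type I error |
|---|---|---|
| One fixed rule (p < 0.10 with the outcome) | 6 or 10, explaining 0–40% of variance | 4.8–5.6% |
| Single-rule selection, second set of simulations | 15–40 | 4.7–5.3% |
| Smallest p over thresholds 0.01, 0.05, 0.10, 0.20 and all candidates | 6 or 10, explaining 0–40% | 5.7–8.1% |
| Smallest p over no covariates, thresholds 0.05, 0.10, 0.20 and all candidates | 15–40 | 9.2–10.3% |
| Smallest p over all 2⁵ = 32 subsets | 5, explaining 0 / 20 / 40% | 6.8 / 11.2 / 17.0% |

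Runs per setting were 3,000 for the 6-or-10-candidate rows, 6,000 for the 15–40 rows and 1,500 for the subsets. The Monte Carlo standard error near 5% with 3,000 runs is √(0.05 × 0.95/3000) = 0.4 points, so the first two rows do not differ from 5%. Inflation appears only where the reported model is picked by its treatment p-value.

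**Step 3: effect lost if follow-up medications are covariates.**
Let m be the share of the 1-point effect that acts through medication change. The adjusted effect is 1 − m, and power at 72 per group is Φ((1 − m)/0.30 − 1.96).

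| m (assumed) | Adjusted effect | (1 − m)/0.30 − 1.96 | Power |
|---|---|---|---|
| 0 | 1.0 | 1.373 | 91.5% |
| 0.10 | 0.9 | 1.040 | 85.1% |
| 0.20 | 0.8 | 0.707 | 76.0% |
| 0.30 | 0.7 | 0.373 | 64.6% |
| 0.50 | 0.5 | −0.293 | 38.5% |

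The SD is held at 1.8 throughout, so only the loss of effect is counted. With baseline medication values, m plays no part and the first row applies.

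**The case against.** The strongest reply has four parts.

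- **Outcome-based selection does not in itself break the test.** This stands. Step 2 shows that one rule, applied without looking at the treatment result, keeps the error near 5%. A reader might infer that choosing covariates from trial data inflates the error automatically; that is wrong, and the article describes no fitting of several models to report the best. It is also an inference that the association will be judged in the trial's own data. That is the natural reading, but the text gives neither time nor source, and it lets single conditions or treatments enter where an influence is expected beforehand, which points partly to prior knowledge.
- **Nothing says that follow-up medications will be used.** This also stands. Calling a variable a confounder usually implies that it precedes treatment, and re-recording pharmacotherapy may be routine follow-up. A reader might infer that part of the effect will be adjusted away; the text supports only that it could be.
- **Center may be safe.** A reader might infer that center can be dropped because it sits among the selectable confounders. The article equally says that all models will be adjusted for it, which can be read as a commitment to keep it.
- **Lists, thresholds and coding belong in an analysis plan.** True, and their absence is no fault here. But the article does more than leave a gap: it states a selection principle. An analysis plan with a fixed list would depart from that principle, and one that followed it would carry the problem over.

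**Conclusion.** The point holds as a fault in a stated rule, and it should be fixed. The article applies a confounder-selection principle from observational work to its one confirmatory test and leaves criterion, coding and measurement time open.

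The harm is conditional in both parts. If the most favourable model were reported, the type I error would be roughly 6–10% for choices among selection thresholds with 6 to 40 assumed candidates, and up to 17% over all subsets of five covariates explaining 40% of the variance; under a single fixed rule it stays at about 5%. If follow-up medication values entered the model, and 10–50% of the effect ran through medication, power at 72 per group would fall from 91% to between 85% and 39%; with baseline values there is no such loss. Candidate numbers, explained variance and mediated shares are all assumptions. The documents do not support saying that the error rate is inflated as planned or that the effect will be diluted, and the sample size is unaffected.

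**What to change.** Before any outcome data are seen by arm:

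1. Replace outcome-based selection in the primary model with a pre-specified set: baseline SPPB and center (always, as the stratification factor), plus any few baseline prognostic factors that the sponsor chooses to name, with their coding.
2. State that comorbidities and medications, where used, enter at baseline values only, and that no post-randomization variable enters any effectiveness model.
3. Label any model with outcome-selected covariates as a sensitivity analysis.

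The cost is a few sentences of analysis text, with no extra patients or data. Planned power stays at about 91% for 72 per group or better. The one downside is less freedom to adapt the model later.

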### Patient and public involvement

Patients and the public are not involved in the design and implementation of this trial.

## Ethics and dissemination

This study has been approved by the Ethics Committee of the clinical centers and will be conducted in accordance with the European Union (EU) 2016/679 and 2016/680 directives and guidelines. Data will be collected on the Research Electronic Data Capture platform (REDCap) [31, 32]. Site access will be protected by a personal password to ensure data safety and confidentiality. Passwords will be given to the researchers by a data manager of the Italian Society of Gerontology and Geriatrics (SIGG). Each patient will be assigned a unique alphanumeric code to which all the data will be linked. This code will be recorded and stored on an encrypted file. To ensure patient anonymity, data will be pseudo-anonymized following the standard ISO 25237:2017. The study findings will be disseminated through a peer-reviewed publication and at appropriate conferences and scientific meetings and shared more broadly through collaborations with patients with diabetes and their caregiver association at both local and national levels.

## Discussion

Diabetes and its complications are associated with several negative health outcomes that can significantly impact the quality of life and the functional independence of older patients with T2DM. Historically, treatment goals for these patients have primarily focused on glycemic control and management of associated cardiovascular risk factors (i.e., blood pressure and lipids profile control) to reduce microvascular and macrovascular diabetes-related complications, respectively. Nevertheless, older patients with T2DM are particularly complex because of multimorbidity [33], polypharmacy [34], and emerging diabetes complications, including frailty, cognitive impairment, and physical disability [35]. Therefore, management of these patients requires a multidimensional evaluation assessing the multiple determinants of health and a tailored multidomain plan of care [36]; indeed, an aggressive and standardized approach characterized by a strict metabolic control might result in negative outcomes including, but not limited to, severe hypoglycemia, particularly among the frailest [37].

Only recently has the importance of the CGA in implementing goal-driven interventions emerged [10]. However, it has yet to be fully integrated into routine diabetes care for older adults. As a result, there is no solid evidence supporting the effectiveness of CGA-driven interventions in delaying the development of functional impairments and achieving PROs in older patients with T2DM. This study aims to address this gap by evaluating the impact of CGA on the complex care needs of older patients with T2DM. Additionally, we propose that incorporating functional outcomes and PROMs as treatment goals may enhance the management of these patients, aligning therapeutic strategies more closely with their specific needs and preferences. Specifically, we anticipate that this multidimensional approach will help preserve better function and prevent or delay the development of disability and other important adverse health outcomes compared to the usual diabetic care practices.

Diabetes has already been linked to reduced muscle performance, which contributes to walking and functional limitations [29]. Furthermore, poor lower-extremity performance has been associated with several critical clinical endpoints in community dwellers and hospitalized patients [11, 38–40]. Therefore, the functional measure adopted as the primary outcome of the present study could serve not only as a treatment goal but also as a strong indicator of the patient’s quality of life. For this purpose, we selected the SPPB, which is easy and quickly measurable in clinical practice and has already been integrated into the PROMs [41]. Simultaneously, the CGA will contribute to the assessment and optimization of other domains (e.g., cognition, physical and psychosocial health, social-environmental circumstances, and polypharmacy), which may contribute to reducing adverse health outcomes and improving satisfaction among patients and caregivers along the care pathway. To comprehensively assess the effect of CGA-driven care pathway, we incorporated a set of secondary outcomes to capture both physical performance-related events, such as the incidence of sarcopenia, falls and institutionalization, and broader clinical endpoints including HbA1c variations, hospitalization rates, mortality and DAH. These measures aim to explore the wider impact of the intervention on the health status and healthcare utilization in this population. Additionally, patient-reported experiences related to involvement in care and support received will be evaluated to provide insight into the intervention’s impact on care quality and patient satisfaction.

This study has some limitations. Implementation of certain aspects of the intervention will depend on patient initiative, as adherence will not be actively monitored between study visits, and specialist consultations will not be scheduled by the study team. As a result, adherence may vary, potentially affecting the consistency of the intervention. To address this, adherence will be assessed using self-reported data collected during follow-up visits. While this approach is practical, it may be subject to recall bias and reporting inaccuracies, which should be taken into account when interpreting the intervention’s potential impact. Lastly, although the study is adequately powered to detect statistically significant effects for the primary outcome, the secondary outcomes were not included in the power calculations. Therefore, analyses of these secondary outcomes should be regarded as exploratory and hypothesis-generating. This limitation may affect the robustness of findings related to secondary outcomes, warranting cautious interpretation.

This study aims to contribute to cumulating evidence concerning the impact of CGA on patients with T2DM. It will reinforce the routine application of an integrated, multidimensional, and multi-professional approach to individual care planning, thereby strengthening the role of patients and addressing their needs to foster a more personalized, inclusive, and participative form of medicine.

In conclusion, the potential impact of this study may extend to improvements in disease management and patient and caregiver satisfaction, as well as to promoting organizational changes. If successful, our approach could inform changes in the practice of diabetologists by incorporating the functional measures outlined and establishing closer collaboration with geriatricians. In the long-term, these changes may help mitigate functional decline and disability progression in older patients with T2DM, with possible positive economic implications on the healthcare system.

## Data Availability

No datasets were generated or analysed during the current study.

## Abbreviations

ADA: American Diabetes Association.
ADL: Activity of daily living.
CCI: Charlson Comorbidity Index.
CFS: Clinical Frailty Scale.
CGA: Comprehensive Geriatric Assessment.
T2DM: Type 2 diabetes mellitus.
EU: European Union.
GAS: Geriatric Anxiety Scale.
GDS: Geriatric Depression Scale.
IADL: Instrumental Activities of Daily Living.
MNA-sf: Mini Nutritional Assessment short form.
MoCA: Montreal Cognitive Assessment.
MSD: Mediterranean Score Diet.
NYHA: New York Heart Association.
PC-FI: Primary Care Frailty Index.
PREMs: Patient Reported Experience Measures.
PROs: Patient Reported Outcomes.
PROMs: Patient Reported Outcome Measures.
REDCap: Research Electronic Data Capture platform.
SIGG: Italian Society of Gerontology and Geriatrics.
SF-12: 12-item Short Form Health Survey.
SPPB: Short Physical Performance Battery.
